## E.7. Anticipated benefits

We expect that at least half the study participants will benefit, namely those who receive DHA supplements. However they will not know this until the completion of the trial and benefit cannot be guaranteed. Possible benefits to research participants include a better understanding of factors that may affect their health. Special efforts will be made to ensure that all study subjects have access to improved health care, which will be facilitated by routine screening by the study nurses and timely referral to the health facilities.

## E.8. Results with possible clinical implications

Although expected to be infrequent, additional benefits may come from the detection of previously unknown health problems that, with treatment, will result in better future health for participants.

## E.9. Women and minority inclusion in clinical research

Women will be well represented as the study subjects are pregnant women and their infants. We expect that half the children to be born and studied will be female. The population to be studied is of Ladino (mixed Spanish-indigenous) ancestry.

## E.10. Inclusion of children

Children are the focus of this study; child development is the primary outcome.

## E.11. Data and safety monitoring plan (revised)

# A Data Safety Monitoring Committee (DSMC) will be formed with experts well qualified in clinical trials among pregnant women *and infants* who are not affiliated with the study team institutions. Letters of support from [name], Professor of Obstetrics and Gynecology, School of Medicine, University of Alabama, Birmingham, AL, [name], senior epidemiologist, Maternal and Child Nutrition Branch, Division of Nutrition and Physical Activity at the Centers for Disease Control and Prevention, Atlanta, GA and [name], National Institute of Perinatology, Mexico, who have all agreed to serve on the committee have been included in Appendix I. *The Data Safety Monitoring Committee will monitor the study for safety and ensure that human subjects protection is assured during the entire duration of data collection. In particular, the DSMC will pay close attention to any adverse outcomes in a) women during pregnancy and delivery, especially increased bleeding; and b) infants, especially those who are born to women recruited early in the study. The DSMC will have the power to stop the study if required. The DSMC will have frequent (monthly) interactions with the study team and will receive immediate communication of any adverse outcomes via email/fax/telephone. The committee will have access to unblinded data upon request and will have the power to call for meetings with the study investigators (either by telephone conference or in person) and close the study if required at any time.*

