**Exclusion criteria**

- High risk pregnancy: This will be as documented in the clinical record at recruitment and will include history and prevalence of abruptio placentae, any serious bleeding episode in the current pregnancy, gestational diabetes, pregnancy induced hypertension, maternal toxoplasmosis infection during pregnancy, coagulation disorders, thrombocytopenia or chronic vascular, renal or systemic disease and drug use.
- Lipid metabolism (hyperlipidemia) and/or absorption disorders
- Regular intake of fish oil or DHA supplements during pregnancy
- Chronic use of medication for illnesses like epilepsy

Informed consent will be obtained from all subjects following standard procedures (see section E) and women will be free to withdraw voluntarily at any time. All study protocols will be explained to the study subjects and will be approved by the Human Investigations Committees at Emory University and INSP. Supplements packaged in blister packs, will be delivered at home weekly by trained field workers who will also monitor compliance by interview and pill count. *Preliminary data collected from women (n=49) who had recently delivered at the IMSS Hospital in Mexico City revealed that most of them (87.5%) considered weekly supplementation at home desirable and  not invasive. Recent data from the National Nutrition Survey in Mexico have shown that only 13.8% of pregnant women reported consuming any micronutrient supplements[[189]](#endnote-189) in contrast to the high coverage rates (> 80%) that we achieved in our clinical trials in Xoxocotla with daily or weekly home visitsError: Reference source not found.* All subjects will have access to routine prenatal care. Infants will also have access to standard care and will be followed up until 18 months of age. The total duration of follow-up will therefore be 23 months for each mother-child pair.

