**Field Director ([name])**

***Supervisor I (Physician) Supervisor II (Nutritionist) Supervisor III (Psyschologist)***

*FW – Field Workers; PSY – Pyschologists; SW- Social Workers*

Table 5: Details of data collection during prenatal and postnatal follow-up

|  | Prenatal | | | | **Birth** | | **Post-partum (mo)** | | | | | | | | | | | |
| --- | --- | --- | --- | --- | --- | --- | --- | --- | --- | --- | --- | --- | --- | --- | --- | --- | --- | --- |
|  | Baseline (20-24 wks gestation) | | **Intervention** | |  | | **1** | | **3** | | **6** | | **9** | | **12** | | **18** | |
| Sociodemographic characteristics | **X** | |  | |  | |  | |  | |  | |  | |  | |  | |
| Obstetric History | **X** | |  | |  | |  | |  | |  | |  | |  | |  | |
| Supplement consumption |  | | **X** | |  | |  | |  | |  | |  | |  | |  | |
| *Maternal diet* | **X** | |  | |  | |  | | **X** | | *X* | |  | |  | |  | |
| Maternal anthropometry | **X** | |  | |  | |  | | **X** | |  | |  | |  | |  | |
| Maternal Weight | **X** | | **X** | |  | |  | | **X** | |  | |  | |  | |  | |
| Maternal PUFA status | **X** | |  | | **X** | | **X** | | **X** | |  | |  | |  | |  | |
| Gestational age and birth outcomes |  | |  | | **X** | |  | |  | |  | |  | |  | |  | |
| Infant anthropometry |  | |  | | **X** | | **X** | | **X** | | **X** | | **X** | | **X** | | **X** | |
| Infant PUFA status |  | |  | | **X** | |  | | **X** | |  | |  | | **X** | | **X** | |
| Apgar & NBAS scores |  | |  | | **X** | | **X** | |  | |  | |  | |  | |  | |
| *Visual and Brainstem Auditory Evoked Potentials* |  | |  | |  | | *X* | |  | |  | |  | |  | |  | |
| Visual recognition memory and visual attention |  | |  | |  | |  | |  | | **X** | |  | | **X** | |  | |
| Global mental and motor development (Bayley) |  | |  | |  | |  | |  | | **X** | |  | | **X** | | **X** | |
| Infant Diet | |  | |  | |  | | X | | **X** | | **X** | | **X** | | **X** | | **X** |
| Breast milk PUFA | |  | |  | |  | | **X** | | **X** | |  | |  | |  | |  |
| *Home environment* | |  | |  | |  | |  | |  | | **X** | |  | | **X** | | *X* |
| Maternal Intelligence | | **X** | |  | |  | |  | |  | |  | |  | |  | |  |

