#### D.2.2.2. Maternal and Child Anthropometry (*revised)*: Maternal anthropometry will be obtained at recruitment and will include height, weight, mid-arm circumference, and triceps and subscapular skinfold thickness using standard procedures**[[203]](#endnote-203)** by trained workers. Details of maternal weight gain during pregnancy will be obtained from medical records. Weights will be recorded to the nearest 0.1 kg and heights to the nearest 0.5 cm. Length, weight and head circumference of the infants will be measured at birth and at 1, 3, 6, 9, 12 and 18 months of age using standard procedures. Data collectors will be trained in anthropometric techniques, and regular standardizations will be carried out. Measurement of accuracy and precision for all anthropometric measurements will be done using methods recommended by Lohman et al (1988)Error: Reference source not found. The scale will be calibrated twice daily with a known reference weight. All data collection will be done at the study headquarters and will be obtained in duplicate by the same data collector. Children will be weighed using a pediatric weighing scale with a precision of 10 g. Infants will be weighed without clothing at birth and with a minimum of clothing (e.g., undershirt, underpants or dry diaper) for subsequent measurements. The weight of clothing will be adjusted for using a second set of clothing. Recumbent length will be measured using a baby-board (UNICEF, Copenhagen, Denmark). Measurements will be read to the nearest 0.1 cm. Weight-for-age and length-for-age z scores will be calculated using the National Center for Health Statistics reference data**[[204]](#endnote-204)**. Head circumference will be measured at the largest occipitofrontal circumference to the nearest 0.1 cm with a non-stretchable tape.

D.2.2.3. Gestational Age and Birth Outcomes *(revised):* Details of birth outcomes (type of delivery, sex, livebirth, etc) will be obtained from hospital records and will be verified by interview in a 10% sub-sample. Gestational age will be determined at birth using Ballard’s method[[205]](#endnote-205).

D.2.2.4. Long Chain Polyunsaturated Fatty Acid Status (Maternal and Infant): *(revised)*

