**E.4.Potential risks**

We judge the potential risks from data collection to be minimal. No invasive procedures are under consideration except for collection of venous blood and breast milk samples; these procedures are minimally invasive and voluntary. Blood samples will be obtained from a subsample of women and infants following routine practices. Appropriate precautions will be taken to avoid inflicting harm or risk to the well being of the subjects. Subjects detected with severe anemia or other life threatening conditions will be followed up to receive appropriate treatment.

The intervention is itself considered safe and the possibility of adverse effects has been minimized by the use of i) stringent inclusion and exclusion criteria and ii) a safe form (algal) and dosage (200 mg) of DHA. Total DHA intakes will remain within a safe range (< 1 g/d) even when combined with dietary sources. Subjects will be free to withdraw from the study at any time. Any potential adverse effects will be monitored and reported by the study investigators immediately to the Data Safety Monitoring Committee as well as to the Human Subjects Committee at INSP and Emory for appropriate action. Potential risks to participants include mild side effects such as gastric discomfort and the identification of new health problems that may be upsetting to participants. Any such findings will be explained to the participant and appropriate follow-up will be advised. Even though the potential for injury to research subjects due to the risks of the proposed procedures is thus judged to be minimal, all reasonable efforts will be made to minimize these risks through the exclusive use of properly trained and educated research personnel. Individuals who are injured by study procedures will be informed of their rights to and be offered treatment of the injury as part of the informed consent procedure and the prevailing local health policy. Detailed procedures for the notification of any abnormal findings of clinical relevance as well as non-emergency and emergency referrals will be developed and implemented. Being in a clinical setting, all subjects will have access to readily available high quality care at all times. A hot-line will exist for the mothers to refer any adverse effects events at the hospital*.*

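### Increased bleeding is singled out for the DSMC, but no scheduled post-randomisation instrument described in the protocol records bleeding or side effects, so rates by arm cannot be reliably compared

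*Protocol*

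**What the plan says.** Section E.11 gives the DSMC its main safety task: "the DSMC will pay close attention to any adverse outcomes in a) women during pregnancy and delivery, especially increased bleeding". It also names infant outcomes, provides for monthly contact with the study team and access to unblinded data on request, and lets the committee stop the study.

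Section E.4 covers how harms come to light. It states that "Any potential adverse effects will be monitored and reported by the study investigators immediately to the Data Safety Monitoring Committee" and that "A hot-line will exist for the mothers to refer any adverse effects events at the hospital". It names a further harm: "Potential risks to participants include mild side effects such as gastric discomfort". The detail is deferred: "Detailed procedures for the notification of any abnormal findings of clinical relevance as well as non-emergency and emergency referrals will be developed and implemented".

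On collection, D.2.2.3 says "Details of birth outcomes (type of delivery, sex, livebirth, etc) will be obtained from hospital records". Section D.1.2 says supplements are "delivered at home weekly by trained field workers who will also monitor compliance by interview and pill count". In Table 5 the intervention period has two entries, "Supplement consumption" and maternal weight.

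**The concern.** Section B.5.2 explains why bleeding was singled out: an earlier fish-oil trial saw a non-significant tendency (p=0.1) to greater maternal blood loss at birth. Having made this the DSMC's priority, the protocol should say which record supplies it, for which women and when. It sets out the other study measurements in that detail, but not this one.

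A committee that receives only what is volunteered sees numbers of reports. It does not see events among a known number of women observed. Unblinding on request does not repair this, because it adds arm labels to an incomplete list. No later analysis can recover a variable that was not recorded for every woman, so this is a matter for the protocol and cannot be left to a SAP. At stake is whether few reported events in the DHA arm can be told apart from few questions asked.

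**Working it through.** **Step 1. Where could bleeding or side effects be recorded after randomisation?**

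| Source in the protocol | What it is described as recording | Bleeding or side effects named? |
|---|---|---|
| Table 5 (introduced in D.2.1, cited in E.2) | Schedule of measurements from baseline to 18 months | No adverse-event, bleeding or tolerability row |
| Weekly home visits (D.1.2, D.2.1, Team I in Figure 4) | Supplement delivery, compliance by interview and pill count; field workers may refer for care | No symptom question stated |
| Delivery record (D.2.2.3) | Type of delivery, sex, live birth, and an open-ended remainder | Blood loss not named |
| Obstetric history questionnaire (D.2.3.1) | Previous and current pregnancy complications, including bleeding | Yes, but Table 5 schedules it at baseline only, at 20-24 weeks |
| Prenatal check-ups (D.1.3) | Routine care, about 70% coverage per visit | No study bleeding or symptom item stated; Table 5 lists only maternal weight, which D.2.2.2 takes from medical records |
| Outcomes (D.4.2) | Birth outcomes, fatty acid status, growth, development | No safety variable |
| Hot-line and investigator reports (E.4) | Spontaneous or ad hoc reports | Adverse effects in general; no definition, form or schedule |

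The only instrument that names bleeding is completed before supplementation can have had an effect. Every route afterwards is unstructured.

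**Step 2. How much information is at stake?** The protocol gives no figure for bleeding, so there is none to reproduce. What follows is an illustration.

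Inputs from the protocol: 994 pregnancies recruited and 15% lost during pregnancy (D.1.5); two-sided 5% test (D.1.4). The recruitment figure itself reproduces: 676 / (0.85 × 0.80) = 994.

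Deliveries per arm = 994 × 0.85 / 2 = 422.

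Assumptions, not in the protocol: background rates of 3%, 5% and 10%; a true doubling; capture of either all events or half of them, equally in both arms.

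Power by the arcsine method: h = 2·arcsin(√p₂) − 2·arcsin(√p₁); z = h·√(n/2), with √(422/2) = 14.53; power = Φ(z − 1.96).

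| Background rate | Capture | Observed p₁ vs p₂ | h | z | Power |
|---|---|---|---|---|---|
| 3% | all | 3% vs 6% | 0.147 | 2.13 | 57% |
| 5% | all | 5% vs 10% | 0.193 | 2.80 | 80% |
| 10% | all | 10% vs 20% | 0.284 | 4.12 | 98% |
| 3% | half | 1.5% vs 3% | 0.103 | 1.49 | 32% |
| 5% | half | 2.5% vs 5% | 0.133 | 1.94 | 49% |
| 10% | half | 5% vs 10% | 0.193 | 2.80 | 80% |

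Complete recording would make the trial informative about a reasonably common bleeding event. Passive capture gives up much of that, even when under-reporting is equal between arms. If it is unequal, the comparison is also biased, in a direction that cannot be known.

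**The case against.** The strongest case on the other side is that monitoring is under-specified but present. Section E.4 places a reporting duty on the investigators. E.7 promises routine screening by study nurses. D.2.1 places a physician study director at the hospital, and nurses help to monitor birth outcomes. D.1.3 describes frequent prenatal check-ups, so the weekly home visit is not the only regular contact. The birth-outcome list in D.2.2.3 is open-ended and drawn from hospital records, which may well hold blood loss. The instruments sit in Appendix III, which is not shown. The earlier bleeding signal was non-significant, came from fish oil, and is attributed in B.5.2 to EPA. The protocol states no safety hypothesis, and a watch item need not be a powered comparison.

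Much of this stands, and it limits the point. A reader might infer that no form collects bleeding at all, that nobody records it, or that the trial cannot detect it. The documents do not support that. The baseline questionnaire asks about bleeding, reporting routes exist, and hospital records could contain the data. Nor is bleeding the only harm named, since gastric discomfort and adverse infant outcomes also appear.

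The objection does not supply a scheduled item. An open-ended list and an unseen appendix do not tell abstractors to record blood loss for every delivery, and they do not explain its absence from Table 5, D.2.2.3 and D.4.2. Even a watch item needs events and a denominator in each arm before a committee can judge it.

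**Conclusion.** The point holds in this form: the protocol singles out increased bleeding for the DSMC but describes no scheduled post-randomisation instrument, and no Table 5 row, that records bleeding or side effects. Rates by arm cannot then be reliably compared, and an excess cannot be reliably excluded. It does not follow that a bleeding problem would go unseen; a striking one could still surface through the hot-line, investigators or routine care.

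On the assumptions above, halving capture costs about 25 percentage points of power at a 3% background rate (57% to 32%), 31 at 5% (80% to 49%) and 18 at 10% (98% to 80%). The background rates, the doubling and the 50% capture are all assumed. These figures show what is at stake and are not a test that the protocol proposes. The textual finding does not depend on them, but it is limited to what the protocol describes, because the Appendix III forms are not available. The change is worth making: it concerns a safety signal the protocol itself raises, and it cannot be put right after data collection.

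**What to change.** 1. Table 5: add a row for maternal and infant adverse events, marked for the intervention period, birth and the postnatal visits.
2. D.2.2.3: name recorded blood loss or haemorrhage, transfusion and labour complications among the items abstracted from the hospital record for every delivery, with definitions. Caesarean delivery is already covered by type of delivery.
3. Weekly pill-count interview (D.1.2, D.2.1): add a short fixed checklist covering bleeding, gastric symptoms and hospital contact.
4. E.11: provide the DSMC with counts by coded arm. Use women with a delivery record as the denominator for delivery events, and women randomised and visited for weekly events. Show the number unobserved in each arm. Using all randomised women for delivery blood loss would count those lost in pregnancy as event-free and bias the rates downward.

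If the Appendix III forms already hold these items, it is enough to cite them in Table 5 and D.2.2.3 and add the reporting rule.

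Cost: a few items on an existing interview and an existing record abstraction, and one table row. No new visit or procedure is needed. The downside is a slightly longer weekly interview and more minor events to log.

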**F. VERTEBRATE (*no changes)***

None

INSP (*Appendix IV).*

